##### Secondary outcomes

Mean difference in PHQ-9 scores of adolescents at 12 months.Proportion who have visited a doctor at least once between randomisation and 12 months

### Statistical considerations

For high-risk adolescents, assuming a 50% remission rate in the control arm at 12 months based on published data [53], and 30 slum clusters per intervention location, at least 27 subjects per slum cluster are needed to detect a 15% absolute improvement in the intervention arm (65% intervention vs 50% control) at 12 months with 90% power. This assumes a 2-sided significance level of 0.05 and an intra-class correlation coefficient (ICC) of 0.1 based on pilot data [25]. To account for up to 20% of participants lost to follow-up, we will aim to enrol at least 33 participants per slum cluster for a total sample size of 1980 adolescents (60 clusters × 33 adolescents). Assuming a prevalence of 3% of adolescents with depression or increased risk of self-harm/suicide (48), we will therefore aim to screen about 1100 adolescents in each slum cluster. Further assuming that 5% of eligible adolescents will refuse to participate, we aim to screen 1160 adolescents in each slum cluster i.e. a total of 69,600 adolescents (60 slum clusters × 1160 adolescents).

Primary analyses will be conducted at the participant level using either random-effect generalised linear mixed models or generalised estimating equations adjusted for clustering. For the primary outcome, remission at 12 months differences will be assessed using a log-binomial (log link function) or logistic regression (log link function) including a random cluster effect. If using generalised estimating equations, the effect of clustering will be accounted for using a repeated cluster effect with a compound-symmetry variance-covariance structure. The intervention effect will be estimated as odds ratio and corresponding 95% confidence interval.

Sub-group analyses will be conducted according to UPHC-level characteristics (size, location and health service characteristics) and patient-level characteristics (demographic factors and clinical factors e.g. depression severity at baseline). The primary outcome will be assessed at 12 months (and reported as secondary outcomes at 3 and 6 months).

Continuous outcomes such as knowledge and behaviour scores of adolescents will be analysed in a similar manner but using generalised linear mixed model with identity link function in place of logit or log link function and with the baseline value of the score included as a covariate in the model. A pre-specified analysis plan including sensitivity analyses, potential covariate adjustments, analyses for secondary endpoints and detailed assumptions (e.g. missing data handling) will be developed prior to unblinding. To ensure that the analysis is not influenced by potential results, all analyses will initially be programmed using randomly scrambled groups. The real group allocation will be used once the statistical analysis plan is finalised, the database locked, and all analyses programmed.

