### Randomisation

Randomisation will be conducted at the level of the slum cluster, in a 1:1 ratio to intervention or control using a central allocation sequence. Natural remission variation between screening and rescreening may be used if deemed appropriate for stratification prior to randomisation. The clusters will be stratified by location, average remission rate for depression between screened and re-screened population per slum cluster and median population of each slum cluster. The slum cluster selected under each intervention and control arms will be non-contiguous to avoid contamination. The random allocation will be performed using a software-based random number generator by a statistician not involved in study conduct or analysis. To maintain blinding, the unblinded statistician will generate the randomisation list and share it directly with field staff. The blinded study statistician as well as the principal investigator will remain blinded until data lock.

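### The primary models as described do not name the factors used to stratify cluster randomisation; if those factors are prognostic, the intervals are wider than they need be and the test is conservative

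*Protocol article*

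**What the plan says.** - **Protocol article, Randomisation.** Slum clusters are randomised 1:1. "The clusters will be stratified by location, average remission rate for depression between screened and re-screened population per slum cluster" and by median cluster population. The sentence just before makes the natural-remission factor optional, so the final list of factors is not fully settled.
- **Protocol article, Statistical considerations, remission.** The participant-level model is "log-binomial (log link function) or logistic regression (log link function) including a random cluster effect". If estimating equations are used instead, clustering enters as a repeated effect with compound symmetry. The effect is reported as an odds ratio with a 95% confidence interval. No stratification factor is named.
- **Same section, continuous outcomes.** Knowledge and behaviour scores are analysed in the same way but with an identity link and "with the baseline value of the score included as a covariate in the model". Again no stratification factor is named.
- **Same section, later plan.** An analysis plan is to be written before unblinding. It will cover, among other things, possible adjustment for covariates. The article does not say that the stratification factors will be among them.

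**The concern.** Stratified allocation makes the arms alike on the strata, so differences between strata contribute little to the true sampling variance of the treatment effect. A model without the strata does not know this. It still puts the between-stratum differences into the cluster variance and reports a standard error suited to unstratified allocation. Intervals are then too wide and the test rejects less often than its nominal level under the null.

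With 60 clusters, an intra-class correlation of 0.1 and 27 participants per cluster, the between-cluster component is three quarters of the variance of a cluster proportion: 0.1 / (0.1 + 0.9/27) = 0.75. That is the component which cluster-level strata can reduce. One stratifier is the cluster's own early remission rate, which could plausibly predict remission at 12 months, but the article gives no figure for this.

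What is at stake is efficiency and correct interval coverage. There is no claim of bias or of an inflated false-positive rate.

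**Working it through.** **Inputs (Protocol article, Statistical considerations).** The control rate: "assuming a 50% remission rate in the control arm at 12 months". The target: "15% absolute improvement in the intervention arm (65% intervention vs 50% control) at 12 months with 90% power". The error rate and clustering: "2-sided significance level of 0.05 and an intra-class correlation coefficient (ICC) of 0.1". The cluster size: "at least 27 subjects per slum cluster are needed". There are 60 clusters, so 30 per arm at 1:1.

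**Step 1: reproduce the plan's figure with no covariates.**
- Individually randomised size for 50% v 65%, 90% power, two-sided 0.05: 227 per arm.
- Design effect: 1 + (27 − 1) × 0.1 = 3.6.
- Effective size per arm: 30 × 27 / 3.6 = 225.
- Power at 225 per arm: 0.8985, that is 89.9%.

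The stated design therefore reproduces, and it does not depend on adjustment.

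**Step 2: effect of including the strata.** Let Rb be the share of between-cluster variance that the strata explain. This is an assumption; the documents give no value. Relative to the model without strata, the variance is multiplied by

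V = [0.1(1 − Rb) + 0.9/27] / [0.1 + 0.9/27] = 1 − 0.75 Rb.

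The ratio of standard errors (with strata to without) is √V. Under stratified allocation the true variability is close to the smaller standard error, so the unadjusted test rejects under the null only when a standard normal exceeds 1.96/√V in absolute value.

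| Rb (assumed) | V | SE ratio √V | 1.96/√V | Type I error without strata |
|---|---|---|---|---|
| 0 | 1.00 | 1.00 | 1.96 | 5.0% |
| 0.2 | 0.85 | 0.92 | 2.13 | 3.4% |
| 0.4 | 0.70 | 0.84 | 2.34 | 1.9% |
| 0.6 | 0.55 | 0.74 | 2.64 | 0.8% |

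**Step 3: simulation on cluster proportions.** 8,000 trials per scenario; 60 clusters of 26, 2×2×2 strata, 1:1 allocation within strata, between-cluster variance 0.1 × 0.25 on the probability scale.

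| Rb | SE without / with strata | Reduction | Type I error without strata | Power without / with |
|---|---|---|---|---|
| 0.2 | 0.0468 / 0.0430 | 8% | 3.4% | 89% / 92% |
| 0.4 | 0.0469 / 0.0390 | 17% | 2.1% | 92% / 96% |
| 0.6 | 0.0472 / 0.0346 | 27% | 0.8% | 94% / 99% |

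With strata in the model the type I error was about 5%. At Rb = 0 the two powers were 87.8% and 87.7%, so nothing is lost.

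**Step 4: simulation closer to the planned model.** Participant-level logistic estimating equations, 60 clusters of 27, exchangeable correlation, bias-reduced standard errors, 400 runs per scenario.

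| Rb | Mean SE without strata (empirical SD), under the effect | Mean SE with strata (empirical SD) | Type I error without / with | Power without / with |
|---|---|---|---|---|
| 0 | 0.194 (0.179) | 0.201 (0.181) | 0.040 / 0.032 | 0.908 / 0.900 |
| 0.25 | 0.195 (0.162) | 0.186 (0.167) | 0.010 / 0.030 | 0.950 / 0.950 |
| 0.5 | 0.196 (0.146) | 0.167 (0.153) | 0.005 / 0.020 | 0.965 / 0.985 |

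The empirical spread of the estimate is much the same with and without strata. What changes is the reported standard error, which comes closer to that spread. This is corroboration only. The standard errors are somewhat conservative even at Rb = 0. With 400 runs, the Monte Carlo error of a 5% rate is about 1.1 points (√(0.05 × 0.95/400)). The simulated allocation also left a small shift of 0.03 to 0.04 in the unadjusted log odds ratio under the null when Rb was above 0.

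**The case against.** The strongest reply is that nothing has been shown to be left out. The model sentence lists a cluster effect without saying that it is the only term; it does not list the treatment term either. Covariate adjustment is assigned to an analysis plan that is not shown, and a journal article may condense. This stands to the extent that a definite omission cannot be established: the article does not name the factors, and it does not exclude them. It does not dispose of the point. The article names a covariate where it intends one, for continuous outcomes, and what it defers is adjustment in general, with no commitment to the strata.

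Second, the size rests on assumed prognostic strength, and one of the stratifiers is itself optional. Both are true. The range has to be read with its lower end at zero, and the remedy should cover only the factors actually used.

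Two stronger readings are tempting and are not supported:

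- **That the trial is underpowered, or wastes power it needs.** The 90% figure reproduces at 89.9% with no covariate. The gain in power was 3 to 5 points in the cluster-proportion simulation and 0 to 2 points in the estimating-equation simulation for prognostic strata.
- **That leaving baseline PHQ-9 out of the remission model also widens the interval.** In the second simulation, at Rb = 0.25 and with an assumed log odds ratio of −0.4 per standard deviation of baseline score, adding it to a model that already had the strata raised the standard error of the log odds ratio from 0.183 to 0.188 and left power unchanged (0.945 v 0.948). Adjusting for an individual covariate also changes which odds ratio is estimated. So the contrast with the continuous-outcome model is not an inconsistency, and there is no need to replace the stated odds ratio by a standardised effect.

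**Conclusion.** The point holds as a modest and conditional one. The primary models as described carry the clustering, and for continuous outcomes the baseline score, but not the factors by which the clusters are randomised. If those factors explain 20% to 60% of between-cluster variance, including them would cut the standard error of the remission effect by about 8% to 27%, and leaving them out gives a nominal 5% test a true level of roughly 3% to 1%. If they explain nothing, there is no loss.

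These figures rest on the article's intra-class correlation of 0.1 holding before any adjustment for strata, on balanced allocation within strata, and on the assumed range for Rb. They concern remission; no figure is offered for the KAB behaviour score, where the same reasoning applies but the documents give no variance inputs. The error is in the conservative direction, and the planned power does not depend on correcting it. It is an improvement available at no cost, best settled before unblinding so that no later choice between results with and without the strata is open.

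**What to change.** Add one sentence to Statistical considerations and carry it into the analysis plan: the primary remission model and the primary KAB behaviour model will include, as fixed effects, the factors actually used to stratify randomisation, namely location, population stratum and, if it was used, natural-remission stratum, in addition to the cluster effect and, for KAB, the baseline score. The sentence should apply whether the mixed model or the estimating equations are chosen. Keep the odds ratio with its 95% confidence interval as the stated effect measure for remission.

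The cost is that sentence. The factors are known before randomisation and need no new data. With three two-level factors the model spends three further parameters against 60 clusters; when the strata explained nothing, power was 87.8% without and 87.7% with them in one simulation, and 0.908 and 0.900 in the other, a difference within Monte Carlo error (√(0.9 × 0.1/400) = 0.015). The sample size is unaffected.

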### Economic evaluation

A trial-based and a modelled evaluation of long-term costs and outcomes will be conducted from a health system perspective. Intervention costs will include salaries, training, and equipment. A within-trial comparison of costs (e.g. visits, medications) will enable estimation of potential cost-offsets associated with the intervention. Average differences in utility observed between treatment arms will be determined using the Short Form 6-Dimension (SF6D), which will be calculated using the Brazier algorithm [54] from the Short Form 36 (SF36) questionnaire. The SF6D is a utility instrument that is derived from the SF36 which is a standard tool for measuring health-related quality of life in economic evaluations [55]. It includes a specific domain for assessing mental well-being, has routinely been used in adolescent mental health research and is validated for use in India [55]. To capture costs and outcomes beyond the trial, a decision-analytic model will be developed to enable long-term morbidity and quality of life to be simulated. Incremental costs per Quality Adjusted Life Years gained will be determined. Sensitivity analyses will determine the robustness of the assumptions of the model.

### Process evaluation

Processes will be monitored continuously throughout the intervention phase. A formal evaluation will be carried out at the end of the intervention using Michie’s Behaviour Change Theory [56] as the over-arching framework to guide our understanding of the intervention implementation and impact. This theory assesses the capability, opportunity, and motivation of adolescents, PHC workers and doctors to engage with the intervention. The researchers will take a case study approach in which a purposive sample of clusters will be selected. In addition to Behaviour Change Theory, the MRC framework for evaluating complex interventions [57] and the RE-AIM (Reach, Effectiveness, Adoption, Implementation, and Maintenance) framework [58] will be used to evaluate the implementation. Qualitative data about the experiences of the adolescents, community participants, UPHC doctors, NPHW, and other key stakeholders will be gathered by researchers through focus groups and in-depth interviews until thematic saturation is reached. For participants in the mHealth intervention arm, the mHealth system will capture health services usage analytic data to assess intervention fidelity. A mixed methods analysis will be conducted informed by the Medical Research Council UK (MRC) guidelines [57]. The process evaluation will assist in the interpretation of the ARTEMIS study results, to understand barriers and facilitators in implementation of the intervention components, explain what aspects work or need modification in future trials, and evaluate whether the intervention was implemented appropriately, and as planned.

### Trial status

Protocol version – V7, 20 Dec 2021

Protocol submitted to: Clinical Trial Registry of India (CTRI)

Trial status: Study approved by CTRI (Reference Number CTRI/2022/02/040307, http://ctri.nic.in/Clinicaltrials/pmaindet2.php?trialid=47111&EncHid=&userName=ARTEMIS-%20CTRI/2022/02/040307).

Trial registration date: 18 February 2022

Recruitment start date: tentatively after 15th July 2022

Recruitment end date: tentatively before 14th July 2023 (one year following recruitment start date)

### Ethical considerations

The study is approved by the George Institute for Global Health India. Approval of the ARTEMIS project from the Health Ministry’s Screening Committee (HMSC), Indian Council for Medical Research (ICMR) has also been received (ID 2020-9770). The study also received ethical clearance from Research Governance and Integrity Team, Imperial College, London on 8^th^ June 2022 (ICREC Reference number: 22IC7718). Any protocol amendment will be shared with the ethics committee approval. If there are protocol deviations, those will be reported to the trial registry too. Any protocol amendment following the start of the trial will also be reported to the trial registry.

Preliminary discussions about the study and interventions with each ward member, PHC doctors and NPHWs were conducted during the initial slum cluster mapping and household listing exercises. Informed written consent will be obtained from all participants who are aged 18 and 19 years and from parents/guardians of under-aged adolescents (10 to 17 years) along with assent from these underage adolescents, by trained interviewers at the time of screening for high-risk populations and prior to administering the detailed questionnaire at baseline and for focused group discussions and interviews. Any individual identified at imminent risk of suicide at baseline will be advised to seek professional help from a doctor/psychiatrist immediately whose contact details would be provided. All data collection and reporting will be compliant with ICMR guidelines [59]. Independent study monitoring will occur for a subset of participants. Data will be de-identified, stored on George Institute India servers, and held in strict compliance with Good Clinical Practice guidelines using our standard operating procedures for data security, confidentiality, backup, and audit trails. As required, all raw data and any derived datasets will be stored at the George Institute India Hyderabad office for at least 10 years from study completion.

### Adverse event reporting

Serious adverse events will be recorded after the start of the intervention phase. A serious adverse event is defined as death due to any cause in the intervention or control arm, hospitalisation due to psychiatric disorders, or a history of self-harm or attempted suicide during the intervention period. These events will be captured using a standardised case report form and reported to an independent Data Safety Monitoring Committee Chairperson on a monthly basis and Ethics Committee Chairperson within 24 h of the implementing team being aware of the incident. This data will be analysed during the Data Safety Monitoring Committee meetings that will be held on a quarterly basis.

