### Eligible population

#### High-risk cohort

All consenting adolescents aged 10 to 19 years will be eligible for screening for depression, or suicide/self-harm risk. The screening will help to identify both high-risk and non-high-risk cohorts. High risk is defined as presence of at least one of the two conditions:High risk of depression based on PHQ-9 score ≥10.Positive response (score ≥2) to the suicide risk question on the PHQ-9.

Field investigators will continue screening until they have identified about 990 adolescents per location at high risk of depression or self-harm/suicide. This will form the ‘high-risk’ cohort. Because there will be some delay (up to 12 weeks) between screening and randomisation the high-risk adolescents will be rescreened to assess if they still meet the inclusion criteria prior to randomisation as literature suggests that around 25% of individuals initially identified at high risk will no longer meet the high-risk criteria at three months [47]. Only those adolescents who continue to remain at high risk during re-screening will form part of the high-risk cohort.

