### Programme milestones

Ethical approval, site approvals and modification of IEC materials will be completed 15 months after the commencement of the study. Screening of eligible adolescent population and baseline interviews of study participants will be completed by 20 months. Randomisation of PHCs into the intervention and control arm will be done in May 2022. Implementing the intervention (anti-stigma campaign and EDSS decision making), follow-up and endline data collection will be completed by 34 months. Publications will be done to highlight various aspects of the project throughout the project period and especially to share the final results. Findings will also be disseminated to various stakeholders including policy makers at a policy symposium held before the end of the study. The final trial report will be written by the researchers of ARTEMIS guided by the PI and CoIs. Professional writers will not be hired to write the trial report.

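### Serious adverse event recording starts with the intervention phase, so serious events in the up to 12 weeks between a consented positive screen and randomisation have no stated formal recording or reporting

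*Protocol article*

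**What the plan says.** The Adverse event reporting section of the protocol article fixes the starting point: "Serious adverse events will be recorded after the start of the intervention phase". The definition that follows counts "death due to any cause in the intervention or control arm", hospitalisation for a psychiatric disorder, and "a history of self-harm or attempted suicide during the intervention period". Events go on a standard case report form. They are reported monthly to the DSMC chair and, within 24 hours of the team learning of them, to the Ethics Committee chair.

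The High-risk cohort section says that "there will be some delay (up to 12 weeks) between screening and randomisation", and that for this reason "the high-risk adolescents will be rescreened to assess if they still meet the inclusion criteria prior to randomisation". According to Ethical considerations, consent (with guardian consent and assent for those under 18) is taken "by trained interviewers at the time of screening for high-risk populations and prior to administering the detailed questionnaire at baseline". The Intervention components section starts the anti-stigma campaign directly after randomisation.

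Three further sections describe contact that may fall in the wait:

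- **Control arm:** an adolescent with PHQ-9 of 15 or more, or a suicide item score of 2 or more, at screening is advised to seek help at once and given a list of facilities. Health workers are asked to follow up more closely, and the team checks that they did.
- **Both arms:** health workers follow participants' wellbeing. No start time is given.
- **Ethical considerations:** anyone at imminent suicide risk at baseline is advised to seek help immediately.

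**The concern.** The study itself identifies these adolescents as being at risk of depression or suicide, and does so after consent. The events that the plan treats as serious are the ones this group is most exposed to. Yet the recording rule opens only once the intervention is running. If a flagged adolescent died or attempted suicide in week 6 of the wait, the team might well hear of it, but nothing in the article would oblige anyone to record it or tell the Ethics Committee or DSMC. Those bodies could then not judge whether the screening, the referral advice and the wait are acceptably safe. Nor could the trial fully account for those lost between the first screen and randomisation.

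**Working it through.** **Time window.** Setting the sections in order of trial events:

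1. Screening: consent is taken and the adolescent is flagged (Ethical considerations; High-risk cohort).
2. Wait of up to 12 weeks, ending with a rescreen against the inclusion criteria (High-risk cohort).
3. Randomisation, with the campaign starting straight after it (Randomisation; Intervention components).
4. Serious adverse event recording starts (Adverse event reporting).

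A death in step 2 is excluded twice: by the starting point, and because no arm exists yet. A self-harm event or attempt is also excluded twice: by the starting point and by the restriction to the intervention period. A psychiatric admission is excluded at least by the starting point. No other section gives a form or reporting route for step 2.

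**Who has stated contact in step 2.** If the screening trigger under Control arm is read as applying to everyone screened, the group with PHQ-9 of 15 or more, or suicide item of 2 or more, has intensified follow-up. For PHQ-9 of 10 to 14 with a suicide item below 2, only advice to consult and the rescreen are stated, plus the wellbeing follow-up under Both arms if that applies before allocation. All of this is care contact; none of it is safety reporting.

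**Size of the gap.** The plan states no figure for this, so there is none to reproduce. Inputs: 12 weeks (High-risk cohort), and 1,980 adolescents (Statistical considerations, 60 × 33; the High-risk cohort section gives about 990 per location, 2 × 990 = 1,980). Whether 1,980 is counted before or after rescreening is not settled, so both readings are shown. The second uses the plan's own 25% expected to leave the high-risk state by three months.

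- 1,980 flagged: 1,980 × 12/52 = 457 person-years.
- 1,980 remaining after a 25% loss: 1,980/0.75 = 2,640 flagged; 2,640 × 12/52 = 609 person-years.

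Both are ceilings, because they let every adolescent wait the full 12 weeks. With 12 months taken as 52 weeks, the wait is at most 12/(12 + 52) = 19% of the time from screening to the final visit. That is a share of calendar time, not of risk.

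**Possible number of events.** The documents give no rate. Purely as an assumption, take 0.1% to 5% per person-year for death, psychiatric admission or attempt combined:

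- low end: 457 × 0.001 = about 0.5 events;
- high end: 609 × 0.05 = about 30 events.

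The range is too wide to support a point estimate.

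**The case against.** The strongest reply is that the rule is coherent as written. Events before allocation belong to no arm and cannot show whether the intervention does harm, which is the question that the Stopping rule section puts to the DSMC. The article also condenses a full protocol that may handle earlier incidents. The first part stands as far as the arm comparison goes. It does not dispose of the point, because the plan's own definition is not limited to attributable events: it includes all-cause death in the control arm. As to the second part, the article does not leave the matter open; it states a starting point that excludes the wait.

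Some stronger readings are tempting and should not be made:

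- *A reader might infer that the wait is unmonitored.* The Control arm, High-risk cohort and Ethical considerations sections describe advice, follow-up and rescreening. What is missing is formal recording and reporting.
- *A reader might infer a wait of about five months* from Programme milestones, where "Screening of eligible adolescent population and baseline interviews of study participants will be completed by 20 months" and approvals are complete at 15 months. That section does not say when screening starts or that anyone waits throughout, and the High-risk cohort section caps the delay at 12 weeks.
- *A reader might infer that lost events distort the cluster remission rate used for stratification.* No section counts death or non-contact as remission, and the Randomisation section bases the rate on those screened and re-screened. A mismeasured pre-randomisation stratifier would in any case not bias a randomised comparison.
- *A reader might infer that anyone who attempts suicide in the wait disappears from the trial.* Such an adolescent may well rescreen positive and be enrolled. The baseline questionnaire asks about treatment history and stressful events, though not as serious event reporting.

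**Conclusion.** The point holds as a gap in participant-safety oversight that the plan's own rule creates. Between a consented positive screen and the start of the intervention, deaths, psychiatric admissions and suicide attempts have no stated formal recording and no stated route to the Ethics Committee or DSMC. The ceiling is 457 to about 609 person-years, depending on whether 1,980 is counted before or after rescreening and assuming that everyone waits the full 12 weeks. The number of events cannot be derived from the documents. The treatment comparison, power and error rates are not affected. The change is a cheap improvement and is worth making.

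**What to change.** - In Adverse event reporting, start recording at screening consent for every adolescent who screens positive, with the same form and the same 24-hour ethics report. Reword the definition so that deaths are not tied to an arm, nor self-harm and attempts to the intervention period, for events before allocation.
- Give the DSMC the pre-randomisation events as a separate listing, outside the comparison of arms.
- At rescreening, record why any positive screen was not re-assessed, for example death, hospitalisation, moved away or refused.
- State whether the follow-up described under Control arm and Both arms applies before allocation. The Control arm text is triggered by screening, when no arm exists, so heading and trigger need to be reconciled.

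The cost is a short protocol change, earlier use of an existing form, and one extra field at a contact already planned. The downside is more reports before randomisation.
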